### **3.4 Quantification of brain circuits of interest under task fMRI and task-free fMRI**

For each task, each subject's preprocessed data will be entered into a general linear model (GLM) using SPM8 (<https://www.fil.ion.ucl.ac.uk/spm/software/spm8/>). Task-evoked activation is quantified using a generalized linear model (GLM) in which task events are convolved with a canonical hemodynamic response function as implemented in SPM8. In this analysis, a 128s high pass filter is applied to the data, and six realignment parameters are added to the design matrix as confounds. Residuals from these models are saved and used for the estimation of task-free connectivity (see below). Specific contrasts of interest are then computed for each circuit as follows: 1) negative affect circuit: sad > neutral conscious faces; 2) negative affect circuit: threat > neutral conscious faces; 3) negative affect circuit: threat > neutral nonconscious faces; 4) positive affect circuit: happy > neutral conscious faces; 5) cognitive control circuit: NoGo > Go trials. Measures of activation for each region of each circuit are obtained by extracting the average value of the contrast of interest.

To quantify task-based functional connectivity, we compute psychophysiological interactions (PPI) between pairs of regions belonging to the same circuit. For each region in each circuit (PPI seed), we calculate the first eigenvariate of that region's time series and fit a whole-brain first-level GLM as described above, which consists of the psychological variable (task contrast of interest), physiological variable (region time course), and the interaction between psychological and physiological variables (PPI effect of interest). Then, we

compute the average PPI effect of interest in specific regions belonging to the same circuit in accordance with our hypothesized model of circuit dysfunction (PPI targets).

Task-free data are derived following an established procedure. First, the residuals of the task effects are saved from the GLM analysis described above. Then, these residuals are band-pass filtered between 0.08 and 0.009 Hz using FSL and concatenated across tasks. We then calculate from these data the correlation coefficient of the timeseries of each region pair belonging to the default mode, attention, and salience circuits. Finally, these values are converted to Fisher z and used as measures of task-free functional connectivity.

Resting brain-wide connectivity will be quantified by Pearson correlations between brain regions. Localized resting state functional connectivity and activity will be quantified using previously determined parcellations, and provide a means to correct for multiple comparisons. We complement this approach with data-driven graph theoretical analysis to characterize whole-brain within-and between-circuit organization and dynamic time-varying activity functional connectivity.

A unique feature of our image processing system is that quantified circuit measures are expressed in terms of standard deviation units from the mean of a healthy reference sample, and thus are interpretable for each individual. We refer to the resulting measures as “regional circuit scores”.

## **4. Outcomes**

### **4.1 Primary Outcomes**

*Neuroimaging:*

1. FEET (conscious and nonconscious) evoked functional activity and connectivity in negative and positive affect circuits

### **4.2 Secondary Outcomes**

*Neuroimaging:*

1. Task-free intrinsic functional connectivity in default mode, attention, and salience circuits
2. Resting-state circuit activity and connectivity
3. MID evoked circuit activity and connectivity
4. Go-NoGo evoked activity and connectivity in the cognitive control circuit

*Behavioral Measures*

1. WebNeuro

*Self-Report Questionnaires:*

1. CADSS
2. 5D-ASC
3. 21-Item DASS

4. SHAPS
5. DAS
6. MAP-SR
7. DARS
8. BPRS
9. MID Cue Rating
10. Face Likability Rating
11. APEQ
12. VAS
13. SRQ

*Additional Measures:*

1. Steroid hormone assay via saliva collection
2. Qualitative free responses

## **5. Statistical methods**

### **5.1 Statistical methods for primary outcomes**

To assess MDMA-induced acute changes in the regional circuit scores derived from the conscious and nonconscious FEET task, repeated measures linear mixed-effects models (LMMs) will be applied. Each outcome measure will serve as the dependent variable, with Dose (placebo, 80mg MDMA and 120mg MDMA) as a within-subjects fixed effect. Further, to assess whether baseline neural profile could predict distinct MDMA-induced acute changes, a median split approach to stratify participants into the high and low activity or connectivity groups and examine the modulation effect of the group. A separate LMM with Dose and Subgroup and their interaction as fixed effects will be implemented. We will focus on the between-subgroup difference between placebo and 120mg MDMA, as well as between placebo and 80mg MDMA. The inclusion of the 80mg dose enhances understanding of dose-dependent MDMA-induced effects and improves blinding. Covariates will include age, biological sex, and motion parameters if they are found to associate with outcomes. For our primary analysis on the pre-registered circuit measures, we will not perform multiple comparison correction as they measure overlapping constructs and do not meet strict criteria for independent measures. We acknowledge the issue of multiple measures, as the detailed set of assessments may measure overlapping constructs and may not meet strict criteria for independence. An alternative approach involves identifying measures that show significant MDMA-induced effects using a  $p < 0.05$  threshold, examining the correlations among these effects, and selecting the measures with the greatest MDMA-induced effect sizes. Additionally, we propose an exploratory option of using principal component analysis (PCA) to form components from correlated measures to reduce dimensions of our data.

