## **2.5 Interventions**

### *2.5.1 Intervention description*

After baseline visit, each participant will receive placebo, 80mg MDMA HCl, and 120mg MDMA HCl in a randomized order. Given the within-subjects design of the study, each participant will receive all three of the specified doses across the duration of the trial. Drug visits will be scheduled 10-14 days apart to avoid drug carry-over effects. Participants will arrive fasted for drug visits in the morning to reduce the risk of emesis. They will complete a urine drug screen and pregnancy test (if applicable) and have their baseline vitals recorded at the Stanford Center for Cognitive and Neurobiological Imaging, where they will be met by the study clinician. Participants will be instructed to orally ingest pills with water or an electrolyte solution. For safety reasons, pulse, blood pressure, temperature, and oxygen saturation will be monitored and recorded every 30 minutes throughout the drug visit. The total visit time for drug visits will be 6-8 hours.

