### *2.6.2 Concealment mechanism*

With our analysis plan and recruitment goal informing the number of randomization assignments, we will use randomization.com to create a random order dose assignment (80mg, 120mg, and placebo) for each of the 40 study IDs. Study IDs are sequential, starting with 001 and ending with 040.

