## **2.11 Data collection and management**

### *2.11.1 Plans for assessment and collection of outcomes*

Outcomes for the study will be measured via functional neuroimaging data, self-report questionnaires, and behavioral measures. Neuroimaging data will be collected at baseline and each of the drug visits. Self-report questionnaires will be collected at baseline, each of three drug visits, and at 1-week, and 1-month follow ups. Behavioral measures will be collected at baseline and each of three drug visits. Self-report questionnaires will be collected via REDCap. The only exceptions to this method of administration are the Visual Analog Scale (VAS), the Brief Psychiatric Rating Scale (BPRS), and the Clinician-Administered Dissociative States Scale (CADSS), which will be administered verbally by a trained clinician (BPRS and CADSS) or research coordinator (VAS). Collected measures and their descriptions are included below.

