### **5.2 Statistical methods for secondary outcomes**

For the secondary outcomes, similar repeated measures LMMs will be applied as the primary outcomes. Each secondary outcome measure will serve as the dependent variable. Covariates will include age, biological sex, and motion parameters if they are found to associate with outcomes. For our secondary analysis, well-established multiple comparison adjustment methods will be applied. For neuroimaging data, cluster-based correction methods will be used to control the family-wise error rate (FWER). For non-neuroimaging data, False Discovery Rate (FDR) adjustments will be applied to control for false positives. Additionally, we propose an exploratory option of using principal component analysis (PCA) to form components from correlated measures to reduce dimensions of our data.

Correlation analysis and cutting-edge mediation analysis will be used to understand the relation between MDMA induced brain changes and MDMA induced changes in behavioral and experiential measures.

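### The mixed models for this three-period crossover omit drug visit, so any trend over visits stays in the residual and costs precision

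*Protocol*

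**What the plan says.** Design: section 2.5.1 states "After baseline visit, each participant will receive placebo, 80mg MDMA HCl, and 120mg MDMA HCl in a randomized order". There are therefore three drug periods and six possible orders. Section 2.11.1 adds "Neuroimaging data will be collected at baseline and each of the drug visits", and section 2.11.4 repeats the WebNeuro battery at baseline and at each drug visit.

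Order list: section 2.6.2 says the team will "create a random order dose assignment (80mg, 120mg, and placebo) for each of the 40 study IDs". Nothing is said about blocking or about balance over the six orders.

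Models: section 5.1 specifies the primary model "with Dose (placebo, 80mg MDMA and 120mg MDMA) as a within-subjects fixed effect". For the baseline stratification, "A separate LMM with Dose and Subgroup and their interaction as fixed effects will be implemented". On adjustment: "Covariates will include age, biological sex, and motion parameters if they are found to associate with outcomes". Section 5.2 says "similar repeated measures LMMs will be applied as the primary outcomes". No visit, period, session or order term appears in either section.

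The one safeguard related to order is the 10 to 14 days between drug visits in section 2.5.1, which is given as protection against drug carry-over.

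**The concern.** In a crossover, the response can drift from visit to visit for reasons unrelated to dose: practice on WebNeuro, familiarity with the scanner, habituation to the same faces. A model with Dose but no visit has two weaknesses. The drift counts as residual noise, which widens the standard error of every dose contrast. And if one dose happens to fall later than another on average, part of the drift enters that contrast.

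The 10 to 14 day spacing addresses carry-over of drug, not drift of this kind. Because section 5.1 names both the fixed effects and the covariates, this is a stated model that lacks a standard crossover term, and not merely detail left to an analysis plan. Power on the primary dose contrasts is at stake, as is how far a single realised estimate can be trusted.

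**Working it through.** **Inputs from the protocol.** N = 40 (2.10); interim look at N = 17 (5.3); three drug periods and six orders (2.5.1); threshold p < 0.05, uncorrected for primary measures (5.1), taken as two-sided.

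**Assumptions, not in the protocol.** Correlation 0.5 between visits of one participant; true 120mg-minus-placebo effect of 0.45 SD; a linear trend of T SD per drug visit. With total SD 1, the residual variance is 0.5 and the SD of a paired difference is sqrt(2 × 0.5) = 1, so the standardised paired effect is also 0.45. The protocol states no numeric effect or power, so its N cannot be reproduced. N = 40 at 80% power implies (1.960 + 0.842)/sqrt(40) = 0.443, which is why 0.45 is used.

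**1. What stays in the residual.** Within a participant the trend takes the values -T, 0, T, with sum of squares 2T² on 2 degrees of freedom. The Dose-only residual variance is therefore about 0.5 + T², and the standard error of the contrast is sqrt(2(0.5 + T²)/40):
- T = 0: sqrt(1.00/40) = 0.158
- T = 0.3: sqrt(1.18/40) = 0.172 (residual variance +18%)
- T = 0.5: sqrt(1.50/40) = 0.194 (residual variance +50%)

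**2. Power at N = 40** (simulated crossovers, unrestricted order list):

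| Trend per visit | Dose only | Dose + visit |
|---|---|---|
| 0 | 0.80 | 0.79 |
| 0.1 SD | 0.79 | 0.78 |
| 0.3 SD | 0.74 | 0.80 |
| 0.5 SD | 0.63 | 0.79 |

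The Dose-only column agrees with the standard errors in step 1: 0.45/0.172 = 2.62 and 0.45/0.194 = 2.32 on 78 degrees of freedom give 0.74 and 0.63. The right-hand column does not depend on the trend; its one-point differences are simulation noise.

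**3. Chance shift if the list is unrestricted.** Over the six orders, the visit-number difference between two doses is ±1 in four orders and ±2 in two. Its variance is (4 × 1 + 2 × 4)/6 = 2. The mean difference over N participants has SD sqrt(2/N): sqrt(2/40) = 0.224 visits, and sqrt(2/17) = 0.343. At T = 0.3 and N = 40, one SD of imbalance shifts the contrast by 0.224 × 0.3 = 0.07 SD, and 1.96 SD shifts it by 0.13, against a standard error of 0.158 with the trend removed. In 29% of such lists the placebo-first and 120mg-first counts differ by 6 or more. For the Dose-by-Subgroup contrast with 20 per half, the SD of the imbalance is sqrt(2/20 + 2/20) = 0.447 visits.

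**4. Error rate.** Over all lists, mean estimates stay at the true value and Dose-only type I error is about 5% (0.042 to 0.052 across trends). Within the roughly 13% most imbalanced lists at N = 40 it is 0.05, 0.13 and 0.24 for trends of 0.25, 0.5 and 1.0 residual SD per visit (0.18, 0.35 and 0.71 SD on the scale above), against 0.04 with the visit term.

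**5. If the list is as balanced as possible.** The shift almost vanishes, but the residual still carries the trend. At 0.5 residual SD per visit, Dose-only type I error falls to 0.029 and power is 0.71, against 0.78 with the term. Exact balance is impossible, since neither 40 nor 17 is divisible by 3 or 6.

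**The case against.** The strongest reply is that randomised order already protects the inference. That stands. A reader might infer that the dose contrasts are systematically biased or that false positives are inflated. The design does not support either: over the randomisation the estimator is unbiased and the test keeps its level. The shift is a matter of the list actually drawn.

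A reader might also infer that the list is known to be unbalanced. Section 2.6.2 is silent on this, so the 0.22 and 29% figures apply only if the list is unrestricted.

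Nor is the relative shift worse at the N = 17 look. Both the shift and the standard error scale as 1/sqrt(N), so their ratio is the same: 0.224T/0.158 and 0.343T/0.243 both equal about 1.41T.

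The trend is an assumption; the protocol mentions neither habituation nor practice. Two design features may keep it small. The FEET measures are within-session contrasts against neutral faces (3.4), so drift common to all faces cancels. And baseline is not a level of Dose, so the change from first to second exposure never enters the dose contrasts. Below about 0.25 residual SD per visit the effect is minor.

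Finally, an analysis plan may add the term. This stands only in part, because section 5.1 already lists the model's effects and covariates and visit is not among them.

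**Conclusion.** The point holds as a loss of precision, with a possible chance shift on top. The fixed models omit a term that a three-period crossover with repeated tasks should carry. If there is a trend over the drug visits, power for the 120mg-placebo contrast falls by about 6 points at 0.3 SD per visit and about 16 at 0.5 SD; at 0.1 SD or less there is nothing to gain. These sizes rest on correlation 0.5, a paired effect of 0.45, a linear trend and an unrestricted list at N = 40, none of which the protocol states. The primary test remains valid on average, so this should be fixed but is not a fatal flaw.

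**What to change.** Add drug visit (1, 2, 3) as a categorical fixed effect to every mixed model in sections 5.1 and 5.2, including the Dose-by-Subgroup models. Commit to it now: section 2.6.4 has the analysts unblinded, so the term should not be left to a choice made after results are seen.

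State whether the order list is balanced over the six orders, and report the number of participants per order. For study IDs not yet assigned, orders may be drawn in blocks containing all six sequences. Balancing is a complement to the visit term and does not replace it (step 5 of the working).

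Cost: two of 78 within-subject degrees of freedom (120 observations, less 40 participants and 2 for Dose). If there is no trend, this is about 1 power point at N = 40 (0.786 to 0.775) and about 3 at N = 17 (0.775 to 0.749), with the effect set for nominal 80% power at each N. No extra data are needed.

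### Section 5.1 leaves the primary FEET circuit measures uncorrected because they are correlated, which does not justify it; in 5.2 the cluster correction does not fit the secondary imaging outcomes that are single numbers

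*Protocol*

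**What the plan says.** **Primary outcomes.** Protocol 4.1 names one composite item: "FEET (conscious and nonconscious) evoked functional activity and connectivity in negative and positive affect circuits". Section 3.4 lists four FEET contrasts (sad, threat and happy for conscious faces, threat for nonconscious faces), among them "negative affect circuit: threat > neutral nonconscious faces; 4) positive affect circuit: happy > neutral conscious faces". Scores are formed region by region: "Measures of activation for each region of each circuit are obtained by extracting the average value of the contrast of interest". Connectivity is scored for pairs of regions within a circuit.

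**Primary analysis (5.1).** "Each outcome measure will serve as the dependent variable, with Dose (placebo, 80mg MDMA and 120mg MDMA) as a within-subjects fixed effect". A second model adds a median-split subgroup and its interaction with Dose, read at 120 mg versus placebo and at 80 mg versus placebo. On multiplicity the text is explicit: "we will not perform multiple comparison correction as they measure overlapping constructs and do not meet strict criteria for independent measures". It then offers an alternative that starts by "identifying measures that show significant MDMA-induced effects using a" threshold of p < 0.05 and ends by "selecting the measures with the greatest MDMA-induced effect sizes". Principal component analysis is mentioned as an exploratory option. The protocol names no single primary measure and no order of testing.

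**Secondary analysis (5.2).** Each secondary outcome is also the dependent variable of a mixed model. Here correction is promised: FDR for non-imaging data, and "For neuroimaging data, cluster-based correction methods will be used to control the family-wise error rate (FWER").

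**The concern.** Independence is not what makes correction necessary. What matters is that several tests each have a chance of a false positive and that any one of them could be reported as a primary result. Bonferroni and Holm hold under any dependence, and a max-T permutation test uses the dependence to lose less power. The protocol's reason therefore supports a milder correction, not none.

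The alternative in 5.1 adds a second problem. Filtering on significance and then keeping the largest effects uses the same data to choose and to estimate, so the retained estimates are biased away from zero.

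The tiers are also inconsistent: the secondary outcomes, where correlated measures are acknowledged too, are corrected, and the primary ones are not. Within the secondary tier, a cluster method needs a map with spatial extent. A region average, a region-pair PPI average or a Fisher z value is one number per person and visit and has no clusters.

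At stake are the error rate behind any primary claim, the size of the effects reported, and whether the error control promised for part of the secondary imaging can be carried out.

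**Working it through.** The protocol states no family-wise error and no number of tests, so there is no figure to reproduce.

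**Inputs**
- Four FEET contrasts (3.4), each with activity and connectivity (4.1): 4 × 2 = 8 measures. One score per contrast and modality is an assumption. Section 3.4 produces scores per region and region pair, but the pre-registered list is not in the document and could be shorter or longer.
- Per-test level 0.05, two-sided: an assumption for the main test. Section 5.1 gives 0.05 only for the alternative approach and does not state sidedness.
- N = 40 (2.10).
- Correlation between measures: not given, so a range is shown, with every pair of measures equally correlated.

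**Family-wise error, independent tests:** 1 − (1 − 0.05)^k
- k = 8: 1 − 0.95^8 = 33.7%
- k = 16: 1 − 0.95^16 = 56.0%

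**Family-wise error, correlated measures** (simulated under no effect of either dose; in the last column both doses share the placebo session):

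| Correlation | 8 measures, one test each | 8 measures, both doses vs placebo |
|---|---|---|
| 0 | 34% | 53% |
| 0.3 | 30% | 48% |
| 0.5 | 25% | 41% |
| 0.7 | 19% | 32% |
| 0.9 | 12% | 21% |

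Separate runs agree to about one percentage point. With one test each, the error falls to 5% only at a correlation of 1, when the eight measures are the same measure.

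**Adding Dose by Subgroup.** Two contrasts on 8 measures are 16 further tests. If they are treated as independent of the main tests (an assumption) and behave like the last column at correlation 0.5, the total is 1 − (1 − 0.41)² = 65%.

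**Selection step.** At N = 40 a paired effect reaches p < 0.05 when it exceeds 2.023 / √40 = 0.32 SD (t with 39 degrees of freedom). Under the null with one contrast, the largest of 8 absolute effects, given that at least one passes, averages about 0.38 SD. This hardly changes with the correlation. It is an average over null data only, so it shows how large an effect the rule reports when there is none.

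**With correction.** Bonferroni over 8 tests uses 0.05 / 8 = 0.00625. The simulated family-wise error is 5.0%, 4.0%, 3.1% and 1.9% at correlations 0, 0.5, 0.7 and 0.9, so control holds throughout.

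**Section 5.2 against 3.4.** The cognitive control contrast (NoGo versus Go) is scored as region averages and region-pair PPI averages. Task-free connectivity is a Fisher z per region pair. Each is then a mixed-model outcome. None has the spatial extent that cluster inference requires. By contrast, 3.4 defines no regional score for MID, and it describes brain-wide resting connectivity with parcellations as a means of correction.

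**The case against.** The strongest defence is that this is a mechanistic study meant to characterise effects, that 5.1 openly acknowledges multiplicity and offers principal components, and that adjustment details often sit in an analysis plan. The point about aim has weight: a descriptive label would be a legitimate answer. But 5.1 does not leave the matter open. It makes a decision and gives a reason, and the reason is wrong.

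Several stronger readings are tempting and are not supported.
- A reader might infer that at least 16 main-effect tests are planned. Section 5.1 enters Dose as one three-level factor and names the two comparisons with placebo only for the subgroup model. One Dose test per measure is therefore the smaller documented count.
- A reader might infer that the primary set is every region and region pair. The no-correction sentence refers to pre-registered measures, and that list cannot be seen here.
- A reader might conclude that a positive primary finding is likely even with no drug effect. At correlations of 0.5 to 0.7 the chance is 19–25%, or 32–41% with two dose contrasts. It passes one half only with near-independent measures and two contrasts, a longer list, or the interaction tests added in.
- A reader might conclude that no secondary imaging outcome has usable control. Cluster methods could serve voxelwise MID or whole-brain resting-state maps, and 5.2 also commits in general terms to established adjustment methods. The mismatch is clear only for the scalar scores.
- The protocol calls the selection rule an alternative and does not say that its output will be the headline result.

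**Conclusion.** The no-correction rule in 5.1 is wrong as written and should be changed, because it governs the primary claim. Under the assumptions of eight equally correlated measures tested at 0.05, the family-wise error is 19–34% with one Dose test each and 32–53% with both doses against placebo, over correlations from 0.7 to 0. The Dose by Subgroup tests raise it further. The exact figure depends on a list and a correlation that the protocol does not give, but no correlation below 1 brings it to 5%.

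The select-the-largest alternative would report about 0.38 SD on average from null data whenever any of the eight measures passes the filter. The mismatch in 5.2 is real but narrower: it covers the Go-NoGo regional and region-pair scores and the task-free Fisher z pairs. On its own it would be a minor clarification.

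**What to change.** 1. **5.1, main effect.** Replace the no-correction sentence with Holm, or max-T permuting dose labels within participant, across the pre-registered FEET measures for the Dose effect, and list those measures. If ordered testing is preferred, test 120 mg versus placebo first and then 80 mg, and state how one step opens the next. A simple valid version gives each of 8 measures 0.05 / 8 = 0.00625 and tests the two doses in that order within the measure.
2. **5.1, subgroup.** Treat the Dose by Subgroup tests as their own Holm-adjusted family, or label them exploratory. A main-effect max-T does not cover them.
3. **5.1, alternative.** Delete the select-largest-effects step, or label it descriptive and report it without p-values.
4. **5.2.** Use FDR, Holm or max-T for scalar region and region-pair scores, and keep cluster correction for voxelwise maps.

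**Cost.** Wording and a scripted adjustment, with no new data. The price is power. For a paired comparison at N = 40, the standardised effect detectable with 80% power is about 0.45 at p = 0.05. With max-T at correlation 0.5 it is about 0.58 for 8 tests (threshold p = 0.0079) and about 0.62 for 16 tests (p = 0.0040). Overall the range is roughly 0.55–0.62, depending on the number of tests and their correlation. A full Bonferroni split over 16 tests (0.05 / 16 = 0.003125) gives about 0.64.
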